### **Reporting of Adverse Events, Adverse Device Effects and Unanticipated Problems**

The PI and study team will conform to the adverse event reporting timelines, formats and requirements of the IRB and DSMC. If a narrative report is submitted, the following information will be provided to all reviewing entities:

|                            |                                                        |
|----------------------------|--------------------------------------------------------|
| Study identifier           | Current status                                         |
| Study Center               | Whether study intervention was discontinued            |
| Subject number             | The reason why the event is classified as serious      |
| A description of the event | Investigator assessment of the association between the |
| Date of onset              | event and study intervention                           |

Any other events will be recorded and reported in accordance with institutional and federal policies.

If an SAE has not resolved at the time of the initial report and new information arises that changes the investigator's assessment of the event, a follow-up report including all relevant new or reassessed information will be submitted to the IRB and DSMC. The PI will be responsible for ensuring that all SAE are followed until either resolved or stable.

### **Investigator Reporting: Notifying the Penn IRB**

The investigator will submit reports to the IRB within ten working days (with one exception) of events that meet the definition of an unanticipated problem involving risks to subjects or others. Exception: If the adverse event involved a death and indicates that participants or others are at increased risk of harm, the investigator will submit a report to the IRB within three days.

The investigator will submit reports to the IRDSMC in accordance to their current reporting requirements:

All Grade 3 or higher events (AE or SAE) within five business days of knowledge.

All unexpected deaths within 24 hours of knowledge.

All others deaths within 30 days of knowledge. Deaths of subjects off-study for greater than 30 days from the last study treatment/intervention are not reportable.

### **Unblinding Procedures**

Only the PI, co-investigator, and project manager will be blinded to what financial incentive subjects are randomized. If unblinding of members of the research team becomes necessary, we will document the following information in REDCap: why unblinding was necessary, date of approval to unblind from the IRB and DSMC, when unblinding occurred, and how unblinding occurred.

### **Confidentiality**

Information about study subjects will be kept confidential and managed according to the requirements of the Health Insurance Portability and Accountability Act of 1996 (HIPAA). Please refer to our request to waive HIPAA authorization.

### **Data Collection and Management**

Source documents are maintained in PennChart. No source documents will be printed or maintained in paper form at the study site. Data from PennChart will be recorded in Case Report Forms (CRFs) developed within Penn Medicine's REDCap system. The investigator and study team (which includes the project manager, research coordinator, and research assistants) will have access to PHI within PennChart and REDCap. We will label all PHI within REDCap as identifiable information so that de-identified exports are possible. All reports that include identifiable information will be stored on the Department of Family Medicine's secure drive, maintained behind the UPHS firewall. Once data analysis and manuscripts have been published, the databases will be removed from REDCap and the data will be de-identified on the secure drive. This de-identified dataset will be stored for up to five years after analysis is complete and manuscripts have been published.

### **Records Retention**

Once analysis is completed and any manuscripts are published, we will retain personally identifiable information no longer than seven years in accordance with government regulations, applicable policies, and institutional requirements.

### **Study Monitoring Plan**

The Principal Investigator will monitor this study with the research team on a bi-weekly basis. He will review the study progress through regular electronic and in person communication.

### **Auditing and Inspecting**

At the discretion of the DSMC, this protocol will be audited approximately 12-18 months from the first subject enrolled and approximately every other year thereafter for the duration of the study. The Principal Investigator will be notified in advance of the selection of their protocol for review and the cases that have been randomly selected. Three randomly selected subjects or 10% of the total accrual, whichever is higher, will be audited. The committee may alter the frequency of re-monitoring based on the audit findings and degree of deficiencies.

The Principal Investigator will permit study-related monitoring, audits, and inspections by the DSMC and/or IRB, government regulatory bodies, and University compliance and quality assurance groups of all study related documents (e.g. source documents, regulatory documents, data collection instruments, study data etc.). The Principal Investigator will ensure the capability for inspections of applicable study-related facilities. As the Principal Investigator of this study, I accept the potential of inspection by government regulatory authorities and applicable University compliance and quality assurance offices.

## **9. Risk/Benefit Assessment**

### **Risks**

The risks associated with this study are no more than minimal. There is the potential risk of breach of confidentiality. We will minimize this risk by using de-identified information whenever possible and by maintaining all identifiable information on a secure drive and/or in a HIPAA-compliant system (e.g. REDCap). There is also the risk of psychological harm associated with being screened for cancer. We will minimize this risk by communicating the results of the screening test to the subject in a timely fashion and facilitating the scheduling of diagnostic testing if the screening test is positive.

### **Benefits**

If a participant completes and returns the FIT, which is standard clinical care, the subjects will potentially benefit from participation by increasing the chances of identifying colorectal cancer at an early stage. Information learned from this study may benefit society through a better understanding of how to effectively increase the return rate of mailed CRC screening which could in turn increase the rate of CRC screening and reduce the rate of CRC mortality.

### **Risk Benefit Assessment**

The risks associated with this study are no more than minimal. Better knowledge of how to increase mailed screening could potentially address one of the major barriers of accessing care, (i.e. having patients come in for clinical office visits). Additionally, FIT is less invasive than colonoscopy and, according to the USPSTF, considered equally effective if conducted once a year (as opposed to having a colonoscopy once every ten years). For these reasons and those outlined in the above benefits section, the Principal Investigator believes that the risks of participating in the study are outweighed by the potential benefits of participating in the study.

## 1. Abstract

This pilot study is a 4-arm randomized control trial assessing the effectiveness of financial incentives for mailed fecal immunochemical test (FIT) kits in patients between 50 and 75 years of age, who have received care Penn Family Care, are due for screening, and are asymptomatic for CRC. The two arms are: (1) usual care, (2) unconditional incentive, (3) conditional incentive, and (4) lottery incentive.

## 2. Objectives

Primary Objective is to assess the effectiveness of financial incentives to increase the response rates to mailed FIT.

Secondary Objective is to further our understanding of the impact of financial incentives on completing mailed FIT.

Primary Study Endpoint ~~will be an increase in~~ **is the** return rate of completed FITs **within 2 months of outreach between the intervention arms when compared to the control arm.**

Secondary Study Endpoints ~~n/a (the secondary objective is qualitative in nature and thus there is no quantitative endpoint)~~ **include the return rate of completed FITs within 6 months of outreach, the percentage of FIT results that are positive, and the percentage of those positive subjects that receive diagnostic colonoscopy. We will look at rates of participation in FIT or colonoscopy that occur outside the study setting during the study period as an exploratory outcome. We will also evaluate the results of the qualitative survey.**

## 3. Background

Colorectal cancer (CRC) is the second leading cause of cancer death in the United States (US), but CRC is potentially preventable through screening. CRC is most curable when detected at an early stage, but unfortunately, over one-half of tumors are detected at late-stage. Screening is cost-effective and has been a key contributor to the declining US CRC incidence and mortality rates over the past three decades. However, screening is underutilized in the US, particularly in some population groups such as blacks, contributing to racial/ethnic disparities in mortality for CRC.

National guidelines recommend screening in average-risk adults aged 50-75. Microsimulation studies suggest that, with high levels of adherence, screening with fecal immunochemical test (FIT) annually may be comparably effective for reducing the risk of CRC death as screening with colonoscopy every 10 years. However, such high levels of FIT adherence are nearly impossible to achieve without effective programs to overcome barriers to receipt of screening.

FIT is ideally suited for mailed outreach screening. FIT has higher sensitivity and specificity and is more acceptable because of improved collection devices and fewer required samples compared to gFOBT. FIT is specific for human hemoglobin thus eliminating dietary restrictions. FIT's performance characteristics have been studied in many settings. In a recent large US study, OC FIT-CHEK's specificity was 94.9% and its sensitivity for detecting advanced adenomas and cancers was 23.8% and 73.8%, respectively.

In this study, we will be using population-based outreach screening to overcome barriers in CRC screening uptake. Mailed FIT outreach has been used to successfully increase CRC screening uptake in many settings, including in Kaiser Permanente Northern California to increase their screening rates to over 80%. Yet, these types of organized programs are limited by response rates to mailed FIT and the costs of annual outreach. There is an opportunity to leverage an organized approach in a different health system but also evaluate new ways to increase response rate. By evaluating the effectiveness of offering financial incentives paired with mailed outreach screening, we will enhance the public health capacity, and efficiency, to increase CRC screening uptake and reduce preventable death from this disease, particularly in underserved populations.

We will also test behavioral economic engagement incentives. Behavioral economics applies principles from both psychology and economics to human health behavioral practices. People do not dispassionately consider the costs and benefits of the choices they make, but tend to place a disproportionately high value on immediate costs and benefits of their actions. This *present-time bias* typically works against health behaviors, since the benefits are typically delayed, while the cost is immediate. There is a significant and immediate non-monetary cost to getting screened that includes the unpleasant nature of and opportunity cost in performing the test, or fear of the results. Financial incentives have been effective in producing desired behavior actions in a variety of clinical contexts, and have been studied in breast and cervical cancer screening, but evidence for use in CRC screening is limited.

## 4 Study Design

### Design

A single center 4-arm randomized pilot study to assess if the rate of completion of FIT is increased by the addition of financial incentives. Potentially eligible subjects will be identified via a data abstraction by Penn Data Store. We will randomly select patients and conduct an electronic medical record (EMR) review using PennChart to confirm eligibility. We will then randomize 1,080 of remaining eligible patients to one of four arms during the intervention phase.

5. Arm 1: mailed FIT kit ~~(usual care)~~ **(control)**

6. Arm 2: mailed FIT kit + \$10 gift card included in mailing (~~reciprocity~~) (**unconditional incentive**)
7. Arm 3: mailed FIT kit + guarantee of receiving a \$10 gift card if kit is returned within two months (~~loss-aversion~~) (**conditional incentive**)
8. Arm 4: mailed FIT kit + entry in a 1/10 chance lottery to receive \$100 gift card if kit is returned within two months (lottery **incentive**)

All 1,080 subjects will receive the mailed FIT kit. Subjects whose FIT results are not recorded in PennChart will receive a follow-up phone call via Interactive Voice Response (IVR) three weeks after the kit was mailed to the subject. Subjects whose FIT results are not recorded in PennChart will receive a follow-up mailed reminder six weeks after the kit was mailed to the subject. Subjects will receive follow-up regardless of the arm to which they are randomized.

A random subsample of 200 subjects will be called twelve weeks after the kit was mailed to the subject to complete a questionnaire. Verbal consent will be obtained from this subsample. This phone call will occur after the intervention and follow-up phases are completed. Analysis will occur after the subsample questionnaire phase is completed.

## Duration

*Subject duration:* We anticipate it taking the subject no more than 15 minutes to prepare, complete, and mail the FIT.

*Study duration:* We anticipate participant enrollment to occur in batches on a rolling basis, such that each of nine batches will include two months of chart review and sending of FIT kits. Given this in conjunction with a two-month wait period (after the last kit is mailed), and a three month analysis period, we anticipate this pilot project to last 23 months.

## 5. Human Subjects

### Resources Necessary for Human Research Protections

Safety will be monitored on an ongoing basis by the PI and the study team. The PI or designee will review the study charts to evaluate events at each subject interaction to ensure the grade, relationship to the study procedure, expectedness and the course of action for each subject is documented. The PI or Sub-investigator is ultimately responsible for assigning grade and attribution.

**Subjects Enrolled by Penn Researchers 1080**

**Subjects Enrolled by Collaborating Researchers 0**

### Accrual

Patients will not be actively recruited for this protocol. We will submit a data query of Penn Family Care patients from the Penn Data Store based on an electronic EMR algorithm that determines guideline-concordant colorectal cancer screening within PennChart. We will randomize 1,080 subjects. We will randomly select 200 patients from the 1,080 subject population with whom we will contact to conduct the questionnaire.

### Key Inclusion Criteria

5. Between 50 to 75 years old
6. Has ~~received care~~ **had at least two visits** at Penn Family Care **within the past two years**
7. Due for screening
8. Asymptomatic for CRC
9. **Zip code listed in PennChart as part of the subjects' address is within the Philadelphia-Wilmington-Camden Metropolitan Statistical Area**
10. **Have a primary care provider in Penn Family Care**

### Key Exclusion Criteria

15. Has had prior colonoscopy within 10 years, sigmoidoscopy within 5 years, and FOBT/FIT within twelve months of the chart review (We will exclude patients who self-report undergoing any of the above procedures)
16. Has a history of CRC
17. Has a history of other GI cancer
18. Has history of confirmed Inflammatory Bowel Disease (IBD) e.g. Crohn's disease, ulcerative colitis. Irritable bowel syndrome does not exclude patients
19. Has history of colitis other than Crohn's disease or ulcerative colitis
20. Has had a colectomy
21. Has a relative that has been diagnosed with CRC
22. Has been diagnosed with Lynch Syndrome (i.e. HNPCC)

23. Has been diagnosed with Familial Adenomatous Polyposis (FAP)
24. Has anemia (iron-deficient)
25. Has history of lower GI bleeding
26. Has metastatic (Stage IV) blood or solid tumor cancer
27. Has end stage renal disease
28. **Has had congestive heart failure**
29. **Has dementia**
30. **Has cirrhosis or end stage liver disease**
31. Has any other condition that, in the opinion of the investigator, excludes the patient from participating in this study

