### Study Intervention Phase

FIT is an immunological stool-based screening test for colorectal cancer. It tests for the presence of human hemoglobin in feces, which increases sensitivity and specificity while decreasing false positives and false negatives. There are no dietary restrictions and requires no direct fecal handling. This is a laboratory test that is used in clinical care and it is a commercially available device. The FIT brand that will be used for this protocol is the OC-Auto® Personal Use Kit manufactured by Polymedco, Inc. FIT is reimbursed by all major insurance companies, Medicare, and Medicaid. .

Eligible subjects will be randomized to one of four arms during the intervention phase:

5. Arm 1: mailed FIT kit (~~usual care~~) **(control)**
6. Arm 2: mailed FIT kit + \$10 gift card included in mailing (unconditional incentive)
7. Arm 3: mailed FIT kit + guarantee of receiving a \$10 gift card if kit is returned within two months (conditional incentive)
8. Arm 4: mailed FIT kit + entry in a 1/10 chance lottery to receive \$100 gift card if kit is returned within two months (lottery incentive)

270 subjects will be randomized to each arm. The investigator and program manager will be blinded to randomization; the research coordinator and assistants will not be blinded. FIT kits will be mailed to subjects over approximately 18 months. Each kit will include a tube in which to deposit the stool sample, directions on how to collect and mail the sample, a letter about CRC screening, a Labcorp requisition form, and a pre-paid return envelope. All subjects will be asked to return the completed kit within two months of receiving the FIT kit.

In addition to the FIT, subjects randomized to Arm 2 will also receive a \$10 gift card and a note explaining that this gift card is a token of our appreciation for completing the kit. Subjects randomized to Arm 3 will receive a note stating that they will receive a \$10 gift card if they return their completed FIT within two months of receiving the FIT kit. Subjects randomized to Arm 4 will receive a note stating that they will be entered in a 1/10 chance lottery to receive a \$100 gift card if they return their completed FIT within two months of receiving the FIT kit.

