### Sub-Sample Questionnaire Phase

A random subsample of 200 subjects will be selected to complete a questionnaire 9 weeks ( $\pm 3$  days) after they received the mailing. Verbal consent will be obtained from this subsample before the questionnaire is administered. Through this questionnaire, the subjects will be asked to confirm their eligibility (e.g. that they had not had CRC screening within the United States Preventive Services Task Force (USPSTF) CRC screening guidelines) and provide additional demographic and socioeconomic status information so that we can better understand what populations, if any, may be more likely impacted by the financial incentives when engaging in CRC screening. We anticipate these questionnaires to take 15-30 minutes to complete over the phone. The research staff will make no more than three attempts to speak directly with the subject. Based on the Penn Family Care quality improvement initiative where we reached about 50% of patients via phone call, we anticipate reaching approximately 100 subjects to complete this sub-sample questionnaire.

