### Subject Withdrawal

Subjects will be withdrawn from this study if they contact the study team and request to be withdrawn from this study. Withdrawal will not affect subject safety or the subject's care at Penn Family Care.

Subjects may withdraw from the study at any time without impact to their care. They may also be discontinued from the study at the discretion of the Investigator (e.g. subject self-reports previous CRC screening that meets the USPSTF CRC screening guidelines, subject contacts the study team and requests to be withdrawn from the study, etc.). The Investigator may also withdraw subjects to protect the subject for reasons of safety or for administrative reasons. It will be documented whether or not each subject completes the clinical study. No protected health information from PennChart will be maintained on behalf of this study. De-identified demographic information will be maintained for analysis purposes. The below table depicts the timeline of study enrollment described above.

|                              | Pre-screening | Baseline
Day 0 | FU to Mailing
Wk 3 (±3 days) | FU to Mailing
Wk 6 (±3 days) | FU to Mailing
Wk 9 (±3 days) |
|------------------------------|---------------|-------------------|---------------------------------|---------------------------------|---------------------------------|
| EMR review                   | X             |                   |                                 |                                 |                                 |
| Randomization                | X             |                   |                                 |                                 |                                 |
| Mail FIT                     |               | X                 |                                 |                                 |                                 |
| IVR                          |               |                   | X                               |                                 |                                 |
| Mailed reminder              |               |                   |                                 | X                               |                                 |
| Questionnaire
(subsample) |               |                   |                                 |                                 | X                               |

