## 7. Analysis Plan

### Power and Sample Size

Through the PFC quality improvement initiative, we have found the accuracy rate of the EMR algorithm to be approximately 80%. As such, we anticipate 1,080 of 1,350 subjects will be eligible **and randomized**, with 270 subjects enrolled on to each of the four arms in a 1:1:1:1 ratio. We estimate a base return rate for controls to be 15% ~~and a base return rate for the intervention arms to be 25%. We will compare the intervention arms against the control arms but we will not compare one intervention against another intervention.~~ **We will compare each intervention arm to the control and use Bonferroni correction for an alpha of .017 (.05/3) in order to account for three comparisons.** Thus, we have 80% power to detect an absolute 40%-11 **percentage point** increase in response rate using a two-sided Type 1 error rate of 0.05 **0.017**.

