**\*\*New changes from initial protocol notated in bold, parts removed from initial protocol notated in strikethrough**

### Power and Sample Size

Through the PFC quality improvement initiative, we have found the accuracy rate of the EMR algorithm to be approximately 80%. As such, we anticipate 1,080 of 1,350 subjects will be eligible **and randomized**, with 270 subjects enrolled on to each of the four arms in a 1:1:1:1 ratio. We estimate a base return rate for controls to be 15% ~~and a base return rate for the intervention arms to be 25%. We will compare the intervention arms against the control arms but we will not compare one intervention against another intervention.~~ **We will compare each intervention arm to the control and use Bonferroni correction for an alpha of .017 (.05/3) in order to account for three comparisons.** Thus, we have 80% power to detect an absolute ~~40%~~ **11 percentage point** increase in response rate using a two-sided Type 1 error rate of ~~0.05~~ **0.017**.

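### Subjects may be removed on self-reported prior screening after randomization, and the plan does not say that they stay in the primary denominator

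*Supplement*

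**What the plan says.** All references are to the final versions in the Supplement.

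- **Key Exclusion Criteria (section 5).** The criterion on earlier colonoscopy, sigmoidoscopy or stool testing is timed to the chart review and carries the addition "We will exclude patients who self-report undergoing any of the above procedures".
- **Subject Withdrawal (section 6).** The first example of a discontinuation at the investigator's discretion is "subject self-reports previous CRC screening that meets the USPSTF CRC screening guidelines". Whether each subject completes the study is to be documented. The effect of discontinuation on the analysis is not stated.
- **Screening Phase and Consent.** Candidates come from a record query, and eligibility is confirmed by chart review. There is no active recruitment, and a waiver of consent is sought.
- **Study Intervention Phase.** The kit goes out with an arm-specific note or gift card. The investigator and program manager are blinded, but "the research coordinator and assistants will not be blinded".
- **Follow Up Phase.** The week-3 automated call and the week-6 letter go only to subjects who have not returned the kit, by the same rule in every arm.
- **Sub-Sample Questionnaire Phase.** In a random subsample of 200, of whom about 100 are expected to be reached, "the subjects will be asked to confirm their eligibility". The call is placed at week 9 here and in the schedule table, and at twelve weeks under Design.
- **Subject Population(s) for Analysis (section 7 and the final SAP).** The primary analysis is labeled intention to treat, but its population is described as subjects who were randomized and who also completed FIT.

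**The concern.** A criterion applied before allocation cannot bias the comparison between arms. The same criterion applied after allocation can, if the people it removes differ in outcome and if the share removed differs by arm. Both conditions are plausible here.

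On outcome, someone already screened has little reason to return a kit, and the reminders that might prompt a call to the study team reach non-returners only. On arm, subjects know whether they hold a gift card, have been promised one, have a lottery entry or have nothing. That can change whether an already-screened person calls in, ignores the kit or returns it.

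The primary endpoint is a simple proportion, so each non-returner removed raises that arm's rate. If such subjects left the denominator, all return rates would be overstated. Unequal removal would also create or hide part of the difference that the trial is sized to detect.

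**Working it through.** **Inputs from the documents.** 270 per arm; control return rate ("We estimate a base return rate for controls to be 15" percent); target increase 11 points, hence 15% vs 26%; "use Bonferroni correction for an alpha of .017 (.05/3) in order to account for three comparisons"; two-sided test; stated power 80%.

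**Reproducing the plan's figure.** Pooled-variance normal approximation without continuity correction:

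- pooled rate = (0.15 + 0.26)/2 = 0.205
- null SE = √(2 × 0.205 × 0.795/270) = 0.0347
- alternative SE = √((0.15 × 0.85 + 0.26 × 0.74)/270) = 0.0344
- critical value at two-sided 0.017 = 2.387
- power = Φ((0.11 − 2.387 × 0.0347)/0.0344) = 78.4%

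This agrees with the stated 80% to within 2 points.

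**Removing non-returners under the null (removal rates assumed).** With a true 15% in both arms, each arm has 40.5 expected returners and 229.5 non-returners. If a fraction f of non-returners is removed, the observed rate is 40.5/(270 − 229.5f):

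| f | Denominator | Observed rate |
|---|---|---|
| 0 | 270 | 15.00% |
| 0.05 | 258.5 | 15.67% |
| 0.10 | 247.1 | 16.39% |
| 0.20 | 224.1 | 18.07% |

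- Equal f in both arms: both rates rise and the difference is 0.
- Control 0.05, incentive 0.10: 16.39 − 15.67 = +0.7 points.
- Control 0.10, incentive 0.20: 18.07 − 16.39 = +1.7 points, about 15% of the 11-point target (1.7/11).
- Control 0.05, incentive 0: 15.00 − 15.67 = −0.7 points.

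**Error rate and power.** Here the removed share e is of all 270 randomized, all of them non-returners, so the observed rate is p/(1 − e). This is a slightly heavier removal than the same percentage of non-returners. Each row gives the probability of rejecting at 0.017 by normal approximation; the null rows were also checked with 200,000 simulated trials each.

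| True rates | e control / incentive | Observed difference | Rejection probability |
|---|---|---|---|
| 15% / 15% | none | 0 | 0.017 |
| 15% / 15% | 5% / 10% | +0.9 points | 0.021 |
| 15% / 15% | 10% / 20% | +2.1 points | 0.038 |
| 15% / 26% | none | 11.0 points | 78% |
| 15% / 26% | 5% / 10% | 13.1 points | 87% |
| 15% / 26% | 10% / 5% | 10.7 points | 69% |

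**The one planned eligibility question.** About 100 subjects reached over four arms is 25 per arm (25/270 = 9%). If an assumed 20% of them (5 per arm) were non-returners and were removed, the rate would be 40.5/265 = 15.3% instead of 15.0%. Larger shifts would need unsolicited reports, which the plan does not limit.

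**The case against.** A reader might infer from the exclusion criterion that self-report can only be learned after randomization. The documents do not establish that. The criterion is timed to the chart review, and a patient's own account of an outside colonoscopy may already be in the record. Read that way, the sentence only says that self-report counts as evidence, which is a sound pre-randomization rule. This stands for the exclusion criterion. It does not reach Subject Withdrawal, because only someone already in the study can be discontinued.

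A reader might also infer that these subjects do leave the denominator, against the intention-to-treat principle. No section says so, and the intention-to-treat label points the other way. But the sentence carrying that label also requires a completed FIT. Read literally, that would leave only completers in the population, so the label cannot be relied on to settle the matter. Correcting that definition would remove most of this concern.

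That those removed are overwhelmingly non-returners is likewise unproven. The questionnaire sample is random, so it includes returners, and the call falls at or after the end of the 2-month window. The preponderance of non-returners is plausible mainly for unsolicited contacts.

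Finally, the discretion to discontinue belongs to a blinded investigator, the reminder rules are the same in every arm, and unblinded staff are described as assembling mailings, not as deciding discontinuations. This reduces the risk of arm-dependent removal. It does not eliminate it, because subjects know their own offer and decide for themselves whether to call.

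**Conclusion.** The point holds as a gap in the protection of the primary comparison. The plan permits discontinuation after randomization on a ground plausibly related to outcome, and no sentence keeps those subjects in the primary denominator. That bias will occur, or in which direction, is not shown.

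The size depends on assumed removal rates and on treating all removed subjects as non-returners. Under those assumptions the false difference is about 0.7 to 1.7 points in either direction, small beside an 11-point target. Equal removal produces none, and the questionnaire alone would move the rates very little. Type I error rises modestly, to 0.021 or 0.038 in the two unequal null cases shown. Severity is moderate: the effect is probably limited, but it bears on the primary estimate and is hard to settle impartially once results are known.

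**What to change.** 1. In Key Exclusion Criteria, limit exclusion on self-report to what is documented in the electronic record at the pre-randomization chart review.
2. In Subject Withdrawal and in Subject Population(s) for Analysis (protocol and SAP), state that every randomized subject stays in the assigned arm and in the denominator, counted as a non-returner unless a completed FIT is returned within 2 months of outreach. Delete the completed-FIT condition from the population definition.
3. Record and report later self-reports and discontinuations by arm. Exclude these subjects only in a labeled sensitivity analysis.

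With all 270 per arm retained, the null difference is 0 at alpha 0.017, and power for 15% vs 26% remains 78.4%.

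The cost is wording in these sections and a count by arm. The estimated return rates will be slightly lower, because some already-screened people remain in the denominator: 15.0% instead of 15.7% to 18.1% under the assumed removal of 5% to 20% of non-returners.
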